### Recruitment strategies and randomization

2.7

The study population is patients who had Post-stroke Cognitive Impairment with no dementia. We will recruit 360 eligible patients from five hospitals in China: The First Teaching Hospital of Tianjin University of traditional Chinese medicine (TCM), The Changchun hospital of TCM, Changzhi City of Traditional Chinese Medicine affiliated hospital, Changsha central hospital, The Second affiliated hospital of Baotou. Recruitment posters will be used in every participating hospital. We also use the various social media platforms to distribute the trial information. The eligible patients must satisfy the criteria defined below. Patients who express a general interest in taking part in the study will be informed of all necessary information in oral and written form. After fulfilling the criteria and signing the consent, the study personnel will assign the patient to the acupuncturist who is in charge of the patient.

A full-time staff of The First Teaching Hospital of Tianjin University of TCM will randomize all the eligible participants into the AG, NAG, or the WLG in a 1:1:1 ratio by a dynamic random allocation technique.

### Blinding

2.8

Assessors who are masked to treatment allocation and trained will be in charge of baseline evaluation and measurement. Patients who receive acupuncture treatment will not be aware of their group assignment. However, the waiting-list group cannot be blinded. Because different acupuncture treatments are used in AG and NAG, it is impossible to blind the acupuncturists. During the trial period and follow-up phases, the third party and assessors will all be blinded.

## Interventions

3

All the groups receive standard treatment that contains controlling blood pressure, blood glucose, blood lipid, symptomatic treatment.

### Acupuncture group (AG)

3.1

Patients in AG will be given TiaoShenYiZhi acupuncture therapy.^[22]^ To ensure the optimal effects of acupuncture stimulation, all the therapists are required to have clinical experience of acupuncture treatments for at least 5 years.

Participants will be asked to adopt sitting or supine position according to their condition. Disposable, sterile needles with a diameter of 0.25 mm and a body length of 40 mm (HUATO, Suzhou, China) will be used. A total of 12 acupoints were selected in the acupuncture therapy, including Neiguan (PC6), Renzhong (DU26), Baihui (DU20), Sishencong (EX-HN1), Fengchi (GB20), Wangu (GB12), Tianzhu (BL10), Sibai (ST2), Shenmen (HT7), Fenglong (ST40), Sanyinjiao (SP6), and Taichong (LR3). PC6, GB20, GB12, BL10, ST2, HT7, ST40, SP6 are used bilaterally. The location and manipulations of the aforementioned acupoints are listed in Table 1. All the manipulations will be applied for 1 minute and the needles are retained for 30 minutes. The participants will be provided acupuncture treatments 3 times per week for 3 months.

**Table 1 T1:** Acupoints selected for use in the study.

Acupoints	Location	Manipulation
Neiguan (PC6)	On the forearm, 2 cun above the transverse crease of the wrist, between the tendons of m. palmaris longus and m. flexor radialis	Vertical insertion with a depth of 0.5--1 cun is applied with the twisting, lifting and thrusting technique of the reducing method for 1 minute
Renzhong (DU26)	On the face, at the junction of the upper third and middle third of the philtrum	Oblique insertion with 0.3--0.5 cun in depth toward the nasal septum and heavy bird-pecking needling is applied until tear formation was observed in patients’ eyes.
Baihui (DU20)	On the midline of the head, 5 cun directly above the midpoint of the anterior hairline, approximately on the midpoint of the line connecting the apexes of both ears	Horizontal insertion with 1 cun in depth is applied with small amplitude and high frequency twisting technique of the reinforcing method for 1 min
Sishencong (EX-HN1)	On the head, a group of 4 points, at the vertex, 1 cun respectively posterior, anterior and lateral to BaiHui (DU20)	
Fengchi (GB20)	On the nape, below the occipital, on a level with Fengfu (DU-16), in the depression between the upper portion of trapezius and the sternocleidomastoid	Vertical insertion with a 1--1.5 cun in depth is applied with small amplitude and high frequency twisting technique of the reinforcing method for 1 minute
Wangu (GB12)	On the nape, in the depression posterior and inferior to the mastoid process	
Tianzhu (BL10)	On the nape, 1.3 cun lateral to the mid-point of the posterior hairline and in the depression on the lateral aspect of m. trapezius	
Sibai (ST2)	On the face, directly below the pupil, in the depression at the infraorbital foramen	Vertical insertion with a 0.3--0.5 cun in depth is applied with mild reinforcing-reducing method for 1 min
Shenmen (HT7)	On the wrist, at the ulnar end of the transverse crease of the wrist, in the depression on the redial side of the tendon of m. flexor carpi ulnaris	
Fenglong (ST40)	On the crus, 8 cun superior to the tip of the external malleolus, lateral to Tiaokou (ST38) about 2 finger-breadth lateral to the anterior border of the tibia	Vertical insertion with a depth of 1.0–1.5 cun is applied with the twisting, lifting, and thrusting technique of the reducing method for 1 min
Taichong (LR3)	On the dorsum of the foot, in the depression distal to the junction of the first and second metatarsal bones	
Sanyinjiao (SP6)	On the crus, 3 cun directly above the tip of the medial malleolus, posterior to the medial border of the tibia	Vertical insertion with a depth of 1.0–1.5 cun is applied with the twisting technique of the reinforcing method for 1 min

### Sham acupuncture group (NAG)

3.2

Acupuncture will be performed at 10 non-acupoints. The selection of non-acupoints in NAG are the points locating on non-meridians, but near the acupoints we select in AG, which is a common method in the design of sham acupuncture.^[23]^ Shallow needling method will be used on these non-acupoints, without making sensation of Deqi. The protocol for choosing the non-acupoints are listed and shown in Table 2 and Figure 2. The requirements for acupuncturists are the same as for AG.

**Table 2 T2:** The location of non-acupoints.

Non-acupoint	Location	Manipulation
Non-acupoint 1 (lei Renzhong)	On the face, directly below the right nostril, 0.5 cun next to Renzhong (DU26)	Prick straight and lightly, make the needles hang on the skin
Non-acupoint 2 (lei Sibai)	On the face, directly below the Outside canthus, on a level with Sibai (ST2), in the sutura between upper jaw bone and zygomatic bone	
Non-acupoint 3 (lei Neiguan)	On the palmar side of the forearm, on a level with Neiguan (PC6) and 1 cun radialis to it (between the Pericardium Meridian of Hand-Jueyin and the Lung Meridian of Hand-Taiyin).	
Non-acupoint 4 (lei Shenmen)	On the wrist, at the transverse crease of the wrist, at the midpoint of Shenmen (HT7) and Daling (PC7) (between the Pericardium Meridian of Hand-Jueyin and the Heart Meridian of Hand-Shaoyin).	
Non-acupoint 5 (lei Fengchi)	On the nap, 1 cun below the outside of Tianzhu (BL10)	
Non-acupoint 6 (lei Wangu)	On the nap, 2 cun lateral to posterior median line, at the level of the lower border of the spinous process of the 4th cervical vertebra	
Non-acupoint 7 (lei Tianzhu)	On the nap, 1 cun lateral to posterior median line, at the level of the lower border of the spinous process of the 3rd cervical vertebra	
Non-acupoint 8 (lei Fenglong)	On the crus, 6 cun below Dubi (ST 35), lateral to Shangjuxu (ST37) and two finger-breadth from the anterior border of the tibia	
Non-acupoint 9 (lei Sanyinjiao)	On the crus, at the midpoint of the medial side of the tibia, on a level with Sanyinjiao (SP6)	
Non-acupoint 10 (lei Taichong)	On the dorsum of the foot, in the depression distal to the junction of the third and fourth metatarsal bones, at the level of Taichong (LR3)	

**Figure 2 F2:**
[figure not shown]
Location of the acupoints and non-acupoints used in the study.

### Waiting-list group

3.3

No intervention except standard treatment will be performed in the waiting-list control group in the initial 36 weeks after randomization.

### Follow-up

3.4

After the 12-week intervention period, all participants will enter an additional 24-week follow-up period. Participants will be followed up per 12 weeks since the treatment end. Assessors will contact with the participants by telephone before the follow-up date. If there is no response to the telephone contact for 1 consecutive week, or the patient expresses that he/she does not want to cooperate with the follow-up, he/she will be listed as lost, the follow-up work should be stopped.

Participants will be given acupuncture treatment when the follow-up period is completed, in order to reduce the shedding rate.

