### Exclusion criteria

2.4

Patients will be excluded if they have any one of the following:

(1)Patients were diagnosed as having cognitive impairment before cerebral infarction;(2)Patients were taking medications that may interfere in the efficacy assessment of the study therapies, including cholinesterase inhibitors, cytosolic sodium, or receiving acupuncture to treat cognitive impairment;(3)Patients who are unable to complete assessments during the screening process due to serious mental, cognitive, or emotional disorders;(4)Patients who have severe diseases in the internal organs, including the heart, liver, and kidney;(5)Patients live alone without long-term living partners or caregiver;(6)Women who are pregnant or preparing to pregnant or breast-feeding;(7)Patients who are recruited into other clinical trials which related to acupuncture or cognitive impairment within 1 month.

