### Primary outcome

3.6

The primary outcome of this study is the cognitive function and incidence of PSD.

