## Data management and quality control

5

The third party is fully responsible for the data management of the project. Specific research assistants (RA), who are masked to treatment allocation, will double-enter the data electronically. Data will be collected by medical records, asking patients, participants’ relatives, caregivers, or proxies directly. The personal information of the participants will be kept in specific files with pre-set codes. Entering data into eCRFs and other essential skills were covered during the training session before study commencement.

We will set up a quality control group to guarantee the validity and reliability of results. Every 3 months, members of the quality control group will perform a quality control review at each hospital and produce a report regarding the quality analysis of the research process.

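### One week of unanswered telephone calls is treated like refusal and ends follow-up, so week-24 and week-36 assessments that could still be made are lost

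*Protocol article*

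**What the plan says.** The protocol article, section 3.4 (Follow-up), sets two visits after treatment: "Participants will be followed up per 12 weeks since the treatment end", that is, at weeks 24 and 36. Before each visit, "Assessors will contact with the participants by telephone before the follow-up date". The rule for loss has two triggers. One is silence: "If there is no response to the telephone contact for 1 consecutive week". The other is an expressed wish not to cooperate. The consequence is the same for both: "he/she will be listed as lost, the follow-up work should be stopped". The section closes by offering acupuncture to participants once follow-up is complete, as a retention measure.

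Three other places bear on the rule:

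- Section 2.4 (Exclusion criteria) rules out this group: "Patients live alone without long-term living partners or caregiver".
- Section 5 (Data management and quality control) accepts other informants: "Data will be collected by medical records, asking patients, participants’ relatives, caregivers, or proxies directly".
- Section 3.6 (Primary outcome) names what is exposed: "The primary outcome of this study is the cognitive function and incidence of PSD". Table 3 schedules MoCA, MMSE and CDR at weeks 24 and 36, each within 3 days either side.

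**The concern.** Silence and refusal are different events. A patient who refuses has made a decision that the trial must respect. A patient who does not pick up the telephone for a week may be travelling, in hospital, unwell or confused, and may well be willing to attend later. Giving both the same permanent consequence discards assessments that nobody has declined.

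The population makes this matter more. All participants have cognitive impairment after a recent stroke, and the trial asks whether they progress to dementia. If failing to answer is related to decline, recurrence or admission, the missing data are related to the outcome. The observed week-24 and week-36 results would then differ systematically from those of the randomised groups. The Discussion presents the 24-week follow-up as evidence of long-term effect, so these visits carry weight.

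**Working it through.** **1. What the rule costs in visits.** Take the wording of section 3.4 at face value.

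| First unreachable before | Assessments lost under the rule | Still obtainable if only the visit is marked missed |
|---|---|---|
| Week 24 | Weeks 24 and 36 | Week 36; also week 24 if the caregiver's call succeeds in time |
| Week 36 | Week 36 | Week 36 only if the caregiver's call succeeds in time or a late visit is allowed |

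The clearest avoidable loss is week 36 in patients missed at week 24. Week 12 falls outside the rule.

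**2. The plan's own allowance for loss (section 7.5).** Inputs: 95 per group and 20% dropout.

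- 95 / (1 − 0.20) = 118.75, rounded up to 119 per group.
- 3 × 119 = 357, which reproduces the stated total. Enrolment is 360, or 120 per group.

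**3. Effect of loss on power.** Inputs from section 7.5: difference 0.6 MoCA points, SDs 1.13 and 1.20, one-sided alpha 0.025.

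- Root-mean-square SD = √((1.13² + 1.20²)/2) = 1.166.
- Power = Φ(0.6 / (1.166 × √(2/n)) − 1.96).

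| Loss | n per group from 120 | Power |
|---|---|---|
| 20% | 96 | 94.6% |
| 30% | 84 | 91.6% |
| 40% | 72 | 87.1% |

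Power holds up well, so any harm is mainly bias.

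**4. Why inflation does not deal with bias.** The values here are assumptions, not figures from the documents. Let true PSD incidence be p, loss among decliners a, and loss among the others b. Observed incidence = p(1 − a) / [p(1 − a) + (1 − p)(1 − b)].

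| p | a | b | Total loss | Observed incidence |
|---|---|---|---|---|
| 20% | 20% | 20% | 20.0% | 20.0% |
| 20% | 40% | 15% | 20.0% | 15.0% |
| 20% | 50% | 10% | 18.0% | 12.2% |
| 10% | 40% | 15% | 17.5% | 7.3% |
| 10% | 50% | 10% | 14.0% | 5.8% |

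Total loss never exceeds the planned 20%, yet the incidence within an arm can be unbiased or clearly too low. A larger sample changes none of these percentages.

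**5. Direction of bias between arms.** Suppose lost patients score 1.2 MoCA points below retained ones in every arm (assumed, about one planning SD). An arm's completer mean then exceeds its full mean by loss × 1.2. Start from a true difference of 0.6 in favour of acupuncture.

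| Loss, acupuncture | Loss, waiting list | Observed difference |
|---|---|---|
| 20% | 20% | 0.6 + 0.24 − 0.24 = 0.60 |
| 15% | 25% | 0.6 + 0.18 − 0.30 = 0.48 |
| 25% | 15% | 0.6 + 0.30 − 0.18 = 0.72 |

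The sign depends on which arm loses more, and the documents do not say. These rows also count loss from every cause. Refusal and the withdrawal criteria in section 2.6 contribute too, so the share due to the one-week rule is unknown.

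**The case against.** **The rule may mean less than it says.** Stopping follow-up work could refer to that visit only, and the article does not say whose number is called. Contact lists and numbers of attempts are details that a journal article usually leaves to the full protocol. This stands in part: the lack of a caregiver call in section 3.4 is not itself an error. The consequence, however, is stated. It is joined to refusal in one sentence, and five hospitals would apply it as worded. If only the visit was meant, the text still needs correcting.

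**The inferences about who is lost are not established.** A reader might infer that the rule concentrates missing data in declining patients. That is plausible, but no figures support it. Participants are free of dementia by the MMSE cut-offs at entry, have a Barthel index of at least 60, and do not live alone without a partner or caregiver, so someone else may answer. A reader might also infer heavier loss in the unblinded waiting-list arm. Section 3.4 offers acupuncture after follow-up to improve retention, which gives those patients a reason to stay reachable. Neither inference can be treated as a finding.

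**Proxy information does not recover the endpoint.** Sections 2.5 and 3.8 define PSD by education-specific MMSE cut-offs, and MoCA also requires testing the patient. Caregiver reports could also be influenced by known allocation in the waiting-list arm. This stands fully. The gain from calling a caregiver is reaching the patient, not replacing the test.

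**Conclusion.** The point holds as a defect in a stated rule. One week of non-response has the same permanent consequence as refusal, and on the plain wording a patient unreachable before week 24 is not sought at week 36. Avoidable gaps follow in the week-24 and week-36 MoCA, MMSE and PSD data. They may be related to outcome, and the 20% allowance protects power but not validity.

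The size and direction of bias cannot be given. It would be wrong to conclude that a particular fraction of the 0.6-point effect is at risk: the loss rates and the 1.2-point gap above are assumed, the 0.6 is not tied to week 24 or 36, and the observed difference could move either way or not at all. The conclusion rests on the literal reading of section 3.4 and on the plausible, unquantified link between non-response and decline, recurrence or admission. It is a modest but cheap improvement. It has to be made while follow-up is running, because no later analysis can recover an assessment that was never attempted.

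**What to change.** Amend the paragraph in section 3.4 as follows:

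- Treat non-response and refusal separately. Stop follow-up when the patient refuses it.
- On non-response, record that visit as missed and keep the patient in follow-up.
- Try the caregiver's or cohabitant's number before closing the visit. The eligibility criteria mean that such a contact should normally exist, so it can be recorded at enrolment.
- Attempt the week-36 assessment in every patient who has not refused follow-up, whatever happened at week 24.
- If late assessments are to be allowed, change the 3-day window in Table 3 accordingly and record the actual assessment date.
- Information on dementia or recurrence from caregivers or records may be collected, labelled as supplementary. PSD stays defined by the MMSE.

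The cost is a one-paragraph amendment, a matching edit to Table 3 if late visits are allowed, and some extra calls by the existing assessors.

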### Outcome assessment

3.5

In this trail, most primary and secondary outcomes will be measured at baseline, the end of intervention(12weeks), after an additional 12-week follow-up period (24 weeks) and after an additional 24-week follow-up period (36 weeks). Amyloid-β and fMRI will be measured at baseline and the end of intervention. A summary of all the measures in the trial is summarized in Table 3.

**Table 3 T3:** Outcome measurements at each timepoint.

Study period	Enrolment	Intervention	Follow-up	
STUDY TIMES	The first time	The second time	The third time	The fourth time
TIME POINT	−3d-0	12 wks ± 3d	24 wks ± 3 d	36 wks ± 3d
MoCA	×	×	×	×
MMSE	×	×	×	×
CDR	×	×	×	×
NPI	×	×	×	×
WHOQOL-BREF	×	×	×	×
FAQ	×	×	×	×
β-Amyloid	×	×		
Adverse Reaction/Event		×	×	×
Vital signs	×	×	×	×
Recurrence		×	×	×
Using drugs	×	×	×	×
Laboratory examination	×	×		

### Primary outcome

3.6

The primary outcome of this study is the cognitive function and incidence of PSD.

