### Cognitive function

3.7

For screening cognitive decline, MMSE is the most common used screening scale.^[24]^ It contains domains of orientation, memory, attention, language, and visuospatial ability.^[25]^ However, studies also showed that MMSE has deficiency on detecting mild cognitive impairment (MCI) and clinical signs of dementia.^[26,27]^ It is superior for more advanced stages, meanwhile MoCA is more useful for the mild stages of the cognitive impairment.^[28]^

Thus, we also use MoCA, which is a cognitive screening, diagnostic, and tracking tool with high sensitivity and specificity for detecting MCI,^[28]^ to evaluate the cognitive function. MoCA also has superiority on detecting executive dysfunction compared with the MMSE.^[29]^ It assesses several cognitive domains such as memory, executive function, attention, language, abstraction, naming, delayed recalls, and orientation.^[30]^ In order to avoid false increase of participants’ cognitive-function test results caused by repeated tests, we will use different versions of MoCA, including 7.1, 7.2, 7.3, and basic of MoCA.

We also choose Clinical Dementia Rating Scale (CDR) to evaluate cognitive function. A CDR of 0.5 is established risk states for dementia.^[31]^ Compared with MMSE, although CDR score is not predictive of change in cognitive performance, it is predictive of functional change over time and of conversion to dementia.^[32]^

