### Incidence of PSD

3.8

We will use MMSE, which is the most widely used by frontline physicians, to detecting dementia. Dementia: MMSE score ≤17 (illiteracy), or MMSE score ≤20 (primary school culture), or MMSE score ≤24 (middle school and above).^[33]^

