### Sample size and statistical methods

7.5

The sample size calculation is based on the improvement of Montreal cognitive assessment scale (MoCA) scores, which has a higher sensitivity than MMSE for MCI.^[7]^ According to the similar published articles,^[40]^ the mean difference in MoCA scores between AG and control group (CG) is 1.5, with a standard deviation of 1.13 in AG and 1.20 in CG. According to our previous study, acupuncture treatment can probably improve the MoCA by 0.6 on average compared with control group. Considering a 1-sided significance level of 0.025 and power of 95%, 95 participants are required for each group, as calculated by PASS 11 software. To minimize attrition bias, we assumed the dropout rate of 20%, making it necessary to include at least 357 participants with a 1:1:1 group allocation rate. We plan to enroll 360 participants in total.

Continuous variables are presented as mean (SD) if they obey normal distribution, and paired-sample *t* test will be used in intragroup comparison; if they are not normal distribution, median (quartile interval) [M(IQR)] will present them, and Wilcoxon rank sum test will be used in intra-group comparison; Variance analysis will be used for comparison between groups which is consistent with the normal distribution and homogeneity of variance; if not, then Mann–Whitney *U* test will be used. Group comparisons will then be undertaken using χ^2^ tests for categorical characteristics. Two-sided *P* < .05 represents statistical significance for all the analyses.

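### The primary outcome is unranked (four measures, three visits, three arms, each at two-sided 0.05), so its false-positive rate is not held at 5%, and the planned three-arm test does not isolate acupuncture from sham.

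*Protocol article*

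**What the plan says.** Section 3.6 of the protocol article: "The primary outcome of this study is the cognitive function and incidence of PSD". Section 3.7 gives cognitive function three instruments. It begins with MMSE ("For screening cognitive decline, MMSE is the most common used screening scale"), adds MoCA ("Thus, we also use MoCA, which is a cognitive screening, diagnostic, and tracking tool"), and then adds a third: "We also choose Clinical Dementia Rating Scale (CDR) to evaluate cognitive function". Section 3.8 defines PSD by education-specific MMSE cut-offs: "We will use MMSE, which is the most widely used by frontline physicians, to detecting dementia".

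Section 3.5 and Table 3 schedule MMSE, MoCA and CDR at baseline and at 12, 24 and 36 weeks, and call no visit primary. Section 2.2 sets three arms: acupuncture (AG), sham (NAG) and waiting list (WLG). Section 2.8 says that assessors are masked but that the waiting list cannot be blinded.

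In section 7.5, "The sample size calculation is based on the improvement of Montreal cognitive assessment scale (MoCA) scores", with a difference of 0.6 against a control group that is not identified, although the trial has two. For the analysis, "Variance analysis will be used for comparison between groups" when normality and equal variance hold, and Mann-Whitney U otherwise. The section closes by ruling that two-sided P < .05 "represents statistical significance for all the analyses".

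**The concern.** Naming the primary outcome is the protocol's job. This one names several measures and does not rank them. It then fixes a significance rule that treats every test alike. A later analysis plan that ranked the measures or adjusted the tests would have to depart from that rule, so the problem lies in what is stated and is not detail left for elsewhere.

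Two things are at stake:

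- **Error rate.** Any one of several tests below 0.05 could be presented as the primary result, so the trial-level false-positive rate is not 5%.
- **The question answered.** A three-arm analysis of variance asks whether the three means differ somewhere. It can be significant because both needled arms do better than an unblinded waiting list, with no difference between real and sham needling.

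**Working it through.** **1. What the sample size covers.** Inputs from section 7.5: difference 0.6, SDs 1.13 and 1.20, one-sided 0.025, power 95%, 95 per group, 20% dropout.

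- Mean variance = (1.13² + 1.20²)/2 = 1.358, so SD = 1.166.
- n per group = 2 × 1.358 × (1.960 + 1.645)² / 0.36 = 98.1, rounded up to 99. With SD 1.13 in both arms it is 92.2, rounded up to 93. The plan's 95 lies between.
- Power at 95: 0.6 / √(2 × 1.358/95) = 3.548, and Φ(3.548 − 1.960) = 94.4%, close to the stated 95%.
- Dropout: 95/0.8 = 118.75, rounded up to 119, and 119 × 3 = 357, as stated.

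The trial is thus sized for one two-arm comparison of one measure. One-sided 0.025 and two-sided 0.05 need the same n, so that difference in wording is harmless here.

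**2. Counting tests.** Four measures at one visit, with one three-arm test each, make 4 tests. Over three visits there are 4 × 3 = 12. If the tests were independent, the chance of at least one P < .05 would be 1 − 0.95⁴ = 18.5% or 1 − 0.95¹² = 46.0%. The measures are correlated (PSD is itself a cut on MMSE), so these figures are too high and correlation has to be allowed for.

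**3. Error rate with correlation.** Correlated normal test statistics were simulated for three arms with no true effect (200,000 replicates). The documents give no correlations. The ranges assumed are 0.3-0.7 between measures and 0.6-0.8 between visits. Chance of at least one P < .05:

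- four three-arm tests, week 12 only: about 13-17%
- twelve three-arm tests, all visits: about 25-38%
- AG versus NAG only, four measures, all visits: about 24-37%

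A separate simulation treated PSD as an MMSE cut-off with an assumed 15% event rate at 95 per arm. Over somewhat wider correlations (0.3-0.8 and 0.5-0.8) it gave 13-18%, 25-40% and 23-39%. The result does not depend on treating PSD as a fourth continuous score.

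**4. What the three-arm test detects.** Let AG and NAG be identical and both exceed WLG by d. The noncentrality is 95 × (2/3) × d² / 1.358, with 2 and 282 degrees of freedom and critical F = 3.03.

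- d = 0.2: noncentrality 1.86, probability of significance 21%
- d = 0.3: noncentrality 4.20, probability 43%
- d = 0.6: noncentrality 16.78, probability 96%

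In all three cases acupuncture has no effect over sham.

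**5. Power under a ranked plan.** One AG-versus-NAG test on MoCA at two-sided 0.05 has 94.4% power for 0.6 at 95 per arm (step 1), with a 5% error rate. If alpha is instead split at 0.025 for each comparator, power is Φ(3.548 − 2.241) = 90.4% each.

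**The case against.** The best defence is that the plan points to a lead measure and a lead visit. MoCA is the basis of the sample size and section 3.7 favours it for mild impairment. Week 12 is the end of treatment, and the later visits are follow-up. PSD may be meant as one cumulative event rather than three visit-level tests. A condensed article may also leave the visit, contrast and adjustment to a fuller document. This has some force: it argues for the lower error range. It does not remove the problem, because MoCA is nowhere named the sole primary measure and four three-arm tests at week 12 alone still give 13-17%.

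Three stronger readings are tempting, and the documents do not support them:

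- **That a placebo effect would count as success.** The protocol states no success rule, so only *could* is justified. The 96% also assumes a shared shift as large as the whole planned effect. Smaller shifts give 43% or 21%. Masked assessors also limit one source of bias.
- **That the error rate is 40-68%, or 84%.** Those figures need pairwise tests against both comparators or among all three arms. Section 7.5 does not state such tests for normally distributed data, and NAG versus WLG does not test acupuncture. The 84% further assumes 36 independent tests.
- **That PSD is almost undetectable.** Spreading the Introduction's 19.3% over 10 years at a constant rate gives about 1.5% in 36 weeks. That cohort was not selected for post-stroke cognitive impairment without dementia. In this trial entry requires an MMSE just above the event cut-off, so a one-point fall can be an event. The 1.5% is not a usable forecast. What can be said is that the document gives no sample-size basis for PSD.

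**Conclusion.** The concern holds in this form. The primary outcome is unranked and the blanket P < .05 leaves its error rate uncontrolled. On the readings examined the rate is about 13-17% (week 12, three-arm tests) to about 25-38% (all visits, three-arm tests). AG versus NAG alone over all visits gives 24-37%. The exact figures rest on assumed correlations, but every combination examined is well above 5%.

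The stated between-group test also does not isolate acupuncture from sham. A non-specific benefit shared by both needled arms could meet the stated criterion with probability 21%, 43% or 96% for shifts of 0.2, 0.3 or 0.6, at the plan's SDs and 95 per arm. This should be corrected before any unblinded analysis, because a primary hypothesis chosen afterwards would not be credible.

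**What to change.** In sections 3.6 and 7.5:

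1. Name one primary hypothesis: MoCA at week 12, AG versus NAG, two-sided 0.05.
2. If it is significant, test AG versus WLG on the same measure and visit at 0.05.
3. If that is significant, test PSD incidence, AG versus NAG by week 36, as a key secondary outcome. This keeps dementia prevention, which the Introduction makes part of the primary aim, inside the confirmatory sequence.
4. Treat MMSE, CDR and the other visits as secondary, either Holm-adjusted or labelled not confirmatory.
5. Replace the P < .05 rule for all analyses with this sequence.
6. State which control the 0.6 difference refers to.

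**Cost.** Wording only, with no extra patients, provided that 0.6 is a fair assumption against sham. Power is then 94% per comparison at 95 per arm, or 90% if alpha is split at 0.025 each instead of sequenced. If 0.6 came from a comparison with a non-sham control, power against sham is unsupported and the sample size needs a fresh justification. The real downside is that PSD incidence is no longer co-primary. That changes the standing of a stated aim and is more than a relabelling, so the sponsor should make the choice knowingly.
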